### 3.9. Data Management

Data will be gathered at predefined intervals under the supervision of a committee responsible for monitoring the data, comprised of members from the Department of Physiotherapy at UNIWA.

Physical records, including printed assessment forms and signed consent documents, will be securely maintained at the study site. All records will undergo monthly backups until the end of the trial to safeguard data integrity. Statistical analyses will be performed by the study statistician on the complete dataset once the study has concluded.

## 4. Analytical Approaches for Statistical Evaluation of the Data

Statistical analyses will be performed using the Statistical Package for the Social Sciences (SPSS, version 29; IBM Corp., Armonk, NY, USA). Prior to inferential analysis, data will be screened for completeness and distributional characteristics. The normality of continuous variables will be examined using the Shapiro–Wilk test. Descriptive statistics will be used to present and summarize participants’ characteristics.

To evaluate the reliability of repeated measurements across the assessment time points, intraclass correlation coefficients will be calculated for the primary outcome measures [44].

The primary analysis will focus on determining whether changes in outcome measures over time differ between the experimental groups. Repeated measures 2 × 3 ANOVA with Bonferroni correction will be used to examine interaction effects between group allocation (IMT vs. sham IMT) and time (T1, T2, T3) [44]. Additionally, we will evaluate differences between groups at each time point. Assumptions of homogeneity of variance will be assessed prior to model interpretation. Statistical significance will be set at an alpha level of 0.05 for all analyses.

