## 2. Objectives

The main aim of this randomized controlled trial is to assess whether a structured inspiratory muscle training intervention enhances inspiratory muscle strength, assessed through maximal inspiratory pressure and maximal dynamic inspiratory pressure, in patients with gastroesophageal reflux disease. Secondary objectives include evaluating changes in GERD symptom severity, disease-related quality of life, and pulmonary function following the intervention.

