### 3.5. Participants and Eligibility Criteria

Adults aged 18–70 years with a confirmed diagnosis of gastroesophageal reflux disease by a gastroenterologist are eligible to participate (inclusion criteria). Selection and initial assessment will be done by a physiotherapist [21,22]. Exclusion criteria include pregnancy, previous gastric or duodenal surgery, systemic connective tissue diseases, tuberculosis, and diagnosed mental disorders [23].

Participants’ characteristics: The sample will comprise participants of all genders, including both males and females with diagnosed GERD, from the Attica region. The minimum sample size was determined using the G*Power software (version 3.1.9.7), based on an effect size of 1.3 for MIP reported by Fonseca et al. (2014) [24]. Based on an effect size of 1.3, a statistical power of 0.80, and an α level of 0.05, the minimum required sample size was 22 participants. Accounting for a potential 15% dropout rate, the final minimum sample size was set at 25.

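### The primary test is an omnibus group-by-time interaction with no primary time point or contrast; it does not isolate the training effect, and it is not the test that the sample size appears to be based on

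*Protocol article*

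**What the plan says.** The aim in section 2 is to "assess whether a structured inspiratory muscle training intervention enhances inspiratory muscle strength", measured by MIP and S-index. It gives no time point.

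Section 3.6 sets three assessments: T1 at baseline, T2 directly after the 12-week programme, and T3 at six months, about three months after training ends.

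Section 4 says that the primary analysis asks whether change over time differs between the groups. The method is: "Repeated measures 2 × 3 ANOVA with Bonferroni correction will be used to examine interaction effects between group allocation" (IMT or sham) and time (T1, T2, T3). It then adds: "Additionally, we will evaluate differences between groups at each time point". None of these comparisons is ranked, and no baseline adjustment is stated for them. The Bonferroni correction is mentioned, but not which comparisons it covers.

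Section 3.5 gives the sample size as "based on an effect size of 1.3 for MIP", with "a statistical power of 0.80, and an α level of 0.05", and concludes that "the minimum required sample size was 22 participants". It names the software but no test, between-visit correlation or expected T3 pattern. The abstract plans to enrol 30.

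**The concern.** The interaction pools two questions: whether training raises strength by the end of the programme (T2), and whether any gain lasts after training stops (T3). A significant result says that the two mean profiles are not parallel. It does not say at which visit they differ, in which direction, or by how much.

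The reader must then turn to the by-visit comparisons, where no visit is primary. That leaves room to choose T2 or T3 as the headline once the data are seen. One of these comparisons is at T1, where randomised groups can differ only by chance. The T2 and T3 comparisons are stated without baseline adjustment in a small trial of men and women. Section 3.6.1 itself gives S-index reference means of 159 cmH2O for men and 115.29 cmH2O for women, so a chance imbalance at baseline is a practical matter.

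If the sample size was worked out for a single two-group comparison, the stated 80% power is also not the power of the declared primary test.

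**Working it through.** **1. Reproducing the 22.** Inputs from section 3.5: effect size 1.3, power 0.80, α 0.05. Assumed because not stated: Cohen's d, two-sided, 1:1. For a two-sample t test the noncentrality is d√(n/2) with 2n − 2 df.

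- n = 10 per arm: 1.3 × √5 = 2.91, power 0.785.
- n = 11 per arm: 1.3 × √5.5 = 3.05, power 0.826.

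So 11 per arm, or 22, is the smallest size that reaches 0.80, an exact match. No other test tried gives 22: one-sided t 18, paired t 7, t at α 0.025 26, Mann-Whitney about 24, repeated-measures interaction with f = 0.65 or 1.3 between 4 and 10.

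**2. Power of the declared primary test.** Let the group differences at T1, T2, T3 be 0, d and f·d, where f is the share of the T2 effect kept at T3. With equal correlation r between visits, the interaction F has 2 and 2(2n − 2) df and noncentrality

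λ = (n/2) × Σ(δ_t − mean δ)² / (1 − r).

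The article gives neither r nor f, so both are assumptions, shown as ranges. For d = 1.3:

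- f = 0.5: the differences are 0, 1.3, 0.65 and the sum of squares is 0.845.
- f = 0 or f = 1: the sum of squares is 1.127.

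Example, n = 11, r = 0.5, f = 0.5: λ = 5.5 × 0.845 / 0.5 = 9.30, df 2 and 40, power 0.75.

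**3. Power of a baseline-adjusted T2 contrast.** λ = (n/2) × d² / (1 − r²), with 1 and 2n − 3 df. Example, n = 11, r = 0.5: 5.5 × 1.69 / 0.75 = 12.39, power 0.92. Multiplying λ by 1 − 1/(2n − 2), for chance imbalance in the covariate, gives 11.77 and power 0.90. Both values are shown.

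| n per arm | r | Interaction, half kept at T3 | Interaction, all or none kept | Baseline-adjusted T2 |
|---|---|---|---|---|
| 11 | 0.3 | 0.60 | 0.73 | 0.84–0.86 |
| 11 | 0.5 | 0.75 | 0.87 | 0.90–0.92 |
| 11 | 0.7 | 0.93 | 0.98 | 0.98 |
| 15 | 0.5 | 0.88 | 0.96 | 0.97–0.98 |

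Half retention is the least favourable pattern for the interaction in the range f = 0 to 1.

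**4. Where the order reverses.** With 11 per arm and the T3 effect fully kept or fully lost, the interaction is slightly ahead at high r (T2 contrast computed with the imbalance factor): 0.981 against 0.976 (d = 1.3, r = 0.7), 0.848 against 0.824 (d = 0.8, r = 0.8), 0.745 against 0.701 (d = 0.5, r = 0.9).

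**5. Isolation.** Put the whole effect at T3: differences 0, 0, 1.3. The sum of squares is again 1.127. With n = 11 and r = 0.5, λ = 5.5 × 1.127 / 0.5 = 12.39 and the interaction is significant in about 87% of trials. The T2 contrast is then significant in 5%, its nominal error rate.

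**6. Baseline adjustment of the by-visit comparisons.** Relative to an unadjusted T2 comparison the variance is 1 − r². That is 1 − 0.25 = 0.75 at r = 0.5 (25% lower) and 1 − 0.49 = 0.51 at r = 0.7 (the exact reduction is r² = 0.49; with rounding in the other direction, variance falls to 51% of the unadjusted value).

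**The case against.** The interaction is a legitimate test of the question as section 4 words it, namely whether change over time differs between groups. It includes T1, so the primary analysis does use baseline and removes stable differences between people. Section 2 names no time point, and nowhere does the article say that T2 is the only primary question. All of this stands. A reader might infer that the primary test is wrong in itself or ignores baseline; the article does not support that.

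A reader might also infer that a T2 contrast always has at least as much power. Step 4 shows that it does not. Wide, stable differences between men and women point towards a high between-visit correlation, which is where the power gap closes.

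The planned enrolment is 30, not 22. After 15% dropout, 30 × 0.85 = 25.5 remain, about 12.75 per arm. The interaction then has power of 0.67 to 0.80 at r = 0.3, 0.82 to 0.92 at r = 0.5 and 0.97 to 0.99 at r = 0.7. So the documents do not show that the trial is underpowered; the loss is modest unless the correlation is low.

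The mismatch with the sample size is inferred, since no test is named, and sizing a trial on a simple two-group comparison is common practice. The plan also mentions a Bonferroni correction, though its scope is unclear and it does not make any contrast primary. Model details may sit in a statistical analysis plan that is not shown, and their absence is not counted here. What remains is what section 4 does fix: an omnibus test as primary and an unranked set of by-visit comparisons.

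**Conclusion.** The point holds in a limited form, and its main weight is on interpretation, not power. The declared primary test cannot by itself say whether IMT raised strength relative to sham at the end of training: it has no direction, gives no effect estimate, and can be driven by T3 alone. No contrast is named to fill that gap.

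The stated 22 and 80% fit a two-group comparison at one time point. For the interaction at N = 22, power of 0.80 is not assured unless r is about 0.6 or more. This rests on d = 1.3 at T2, equal correlations between visits, and assumed values of r and T3 retention.

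It would go too far to say that leaving out baseline adjustment discards most of the precision. The omission concerns only the additional comparisons, and the saving in variance is about a quarter at r = 0.5 and about half at r = 0.7.

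**What to change.** Before analysis, revise section 4 as follows:

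- Name the IMT-minus-sham difference in MIP at T2, adjusted for baseline MIP and reported with a 95% CI, as the primary contrast. Obtain it from a mixed model for T2 and T3 with baseline MIP, group, visit and group × visit, or from ANCOVA at T2. Make the T3 contrast secondary.
- Use the same model, each outcome with its own baseline, for S-index, RDQ, Reflux-Qual and spirometry.
- Drop the between-group test at T1.
- In section 3.5, state that the 22 participants and 80% power refer to a two-group comparison at one time point and not to the interaction, once the study team has confirmed that this is what was calculated.

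The cost is small. Baseline, T2 and T3 are already scheduled, so no extra participants or visits are needed, and SPSS 29 can fit the model. Section 3.9 places the analysis after the study has concluded, so the contrast can still be fixed before results are seen. Section 5 says that no further modifications are allowed, so the change may need to be notified to the ethics committee. The one statistical downside is a slight loss of power if correlation is high and the T3 effect is fully kept or fully lost.

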## Abstract

Gastroesophageal reflux disease (GERD) is a common chronic condition mainly caused by the dysfunction of the antireflux mechanism at the gastroesophageal junction. This is composed of the lower esophageal sphincter and the crural diaphragm. Increasing evidence suggests that diaphragmatic dysfunction and reduced inspiratory muscle strength may contribute to the persistence of GERD symptoms. Although respiratory physiotherapy has shown beneficial effects, the role of a structured inspiratory muscle training (IMT) program has not been sufficiently examined. This study aims to investigate the effects of an inspiratory muscle training program on inspiratory muscle strength and secondary clinical outcomes in individuals with GERD. A total of thirty adults with a confirmed GERD diagnosis will be enrolled in a two-arm randomized controlled trial. These volunteers will be randomly assigned either to the experimental group, which will undergo a 3-month inspiratory muscle training (IMT) using tapered flow resistive loading at 40% of maximal inspiratory pressure (MIP), or to the control group, which will receive sham IMT with a consistent low resistance. Primary outcomes will include maximal inspiratory pressure (MIP) and maximal dynamic inspiratory pressure (S-index). Secondary outcomes will assess GERD symptoms, disease-related quality of life, and pulmonary function. Measurements will be performed at baseline, at three months of intervention, and at six months from recruitment (follow-up). IMT is expected to lead to significant improvements in inspiratory muscle strength, symptom burden, and quality of life compared with sham training. This trial will provide novel evidence regarding the role of inspiratory muscle training as a non-pharmacological intervention in the management of GERD. **Trial registration:** ClinicalTrials.gov Identifier: NCT07131397.

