#### 3.6.1. Primary Outcomes

Inspiratory muscle strength is the primary outcome of the study. Maximal inspiratory pressure (MIP) will be used as an indicator of overall inspiratory muscle strength, reflecting the maximum static pressure generated against an obstructed airway. This measure has been chosen for its clinical relevance in identifying diaphragmatic weakness and monitoring adaptations induced by training [34]. The ATS/ERS guidelines recommend performing 3 measurement attempts. According to them, an absolute maximum inspiratory pressure value at the mouthpiece of 80 cmH_2_O usually excludes clinically significant weakness of the inspiratory muscles. In older ages, the limit for men is 60 cm H_2_O and for women, it is 40 cmH_2_O [34]. The measurement of maximum expiratory pressure will be performed using the same equipment, measures the strength of the expiratory muscles and is performed with the patient in a sitting position and closed nose. A maximal inspiratory effort is commanded for 1–2 s and repeated 3–8 times. In women, the normal limit is 120 cmH_2_O of mercury, while in men, it is 150 cm of mercury [35]. In addition, maximal dynamic inspiratory pressure will be assessed using the S-index. The S-index is a new non-invasive method for the dynamic assessment of inspiratory muscle strength. The measurement is performed using an electronic inspiratory muscle training device that applies conical flow resistance as a loading method. The measurement includes 10 maneuvers, with the participant being encouraged to make a maximum effort up to the total lung capacity. At the beginning of the measurement, a warm-up session (one set of 30 breaths at 40% of S-index) has been included to enhance pulmonary function and attenuate the ‘learning effect’ of repeated measurements [27]. This outcome provides information on inspiratory muscle performance under conditions that more closely resemble functional breathing tasks and may be more sensitive to training-related changes than static measurements alone [27,36]. The average value of the S index in healthy populations is 159 cmH_2_O in men and 115.29 cmH_2_O in women [28].

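### MIP and S-index are both primary, each tested at 0.05, with no rule linking them: if either may carry the claim, family-wise error is about 7–10%; if both must succeed, the stated 80% power does not cover the claim

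*Protocol article*

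**What the plan says.** The abstract gives two primary measures: "Primary outcomes will include maximal inspiratory pressure (MIP) and maximal dynamic inspiratory pressure (S-index"). Section 2 (Objectives) describes the main aim as inspiratory muscle strength "assessed through maximal inspiratory pressure and maximal dynamic inspiratory pressure, in patients with gastroesophageal reflux disease". Section 3.6.1, under a plural heading, names a single construct, "Inspiratory muscle strength is the primary outcome of the study". It describes MIP and then brings in the second measure with "In addition, maximal dynamic inspiratory pressure will be assessed using the S-index". No section ranks the two measures, sets a testing order, or says whether one or both must be significant.

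Section 4 describes the main analysis as a repeated measures 2 × 3 "ANOVA with Bonferroni correction will be used to examine interaction effects between group allocation" and time, and closes with "Statistical significance will be set at an alpha level of 0.05 for all analyses".

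Section 3.5 sizes the trial "based on an effect size of 1.3 for MIP", with power 0.80 and alpha 0.05. This gives a minimum of 22, raised to 25 for 15% dropout. The abstract plans to enrol 30. No effect size or power is given for S-index.

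**The concern.** Two unranked primary outcomes, each tested at the full 0.05, leave the primary conclusion undefined in the case that matters most: one outcome significant and the other not. If the trial is then called positive, the investigators have had two chances at a false positive, and the 5% in the text is not the error rate of the claim. If it is called negative, both outcomes were required, and the power statement describes only one of them.

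A split result is realistic. Section 3.6.1 itself suggests that S-index may respond to training more readily than static measures. If the rule is chosen after the results are known, the choice can follow the results.

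**Working it through.** **Inputs.** From the document: two primary outcomes (abstract, 3.6.1); alpha 0.05 for each analysis (section 4); effect size 1.3 for MIP, power 0.80, minimum 22, 15% dropout (3.5); 30 to be enrolled (abstract). Assumed: two-sided tests, 1:1 allocation, and the correlation ρ between the two test statistics, which the document does not give.

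**1. The plan's own figure.** A two-sample t-test (noncentral t, two-sided 0.05, d = 1.3) first reaches 80% power at 11 per arm, so 22 in total, with power 82.6%. The stated 22 is reproduced at the full 0.05. At two-sided 0.025 the same calculation needs 13 per arm, so 26 (power 81.5%). The sample size therefore does not reflect alpha shared between two outcomes.

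**2. Error if either outcome suffices.** Independent tests: 1 − (1 − 0.05)² = 1 − 0.9025 = 0.0975. The upper bound for any dependence is 0.05 + 0.05 = 0.10. For correlated tests the error is 1 − P(|Z₁| < 1.96 and |Z₂| < 1.96) under a bivariate normal with correlation ρ. As a check on the planned analysis, the 2 × 3 group-by-time F test was simulated for two correlated outcomes (30 participants, 20,000 runs, assumed correlation 0.7 between time points):

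| ρ | Bivariate normal | Simulated interaction F tests |
|---|---|---|
| 0 | 9.75% | 9.4% |
| 0.3 | 9.5% | 9.8% |
| 0.5 | 9.1% | 8.9% |
| 0.7 | 8.3% | 8.4% |
| 0.8 | 7.8% | 7.9% |
| 0.9 | 7.0% | 7.2% |

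In the simulation a single outcome rejected in 4.9–5.1% of runs, so the excess comes from having two outcomes.

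**3. Error and power if both are required.** A false joint claim needs the outcome with no effect to reject, so the error is at most 5%. Joint power is the difficulty. Suppose S-index also had d = 1.3 (an assumption, since the document gives none). With 22 analysed, joint power would lie between 0.826 × 0.826 = 0.68 (independent) and 0.826 (perfect correlation).

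**4. Fixed sequence, MIP then S-index.** If MIP has no effect, any false claim must begin with a MIP rejection, at most 5%. If MIP has an effect and S-index does not, a false claim needs an S-index rejection, again at most 5%. MIP is still tested at 0.05, so its power stays at 82.6% with 22 analysed.

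**5. Splitting alpha, 0.025 each.** Family-wise error is at most 5% (simulated 3.6–4.9%). MIP power at d = 1.3 is 73.0% with 22 analysed, 79.6% with 25 and 87.6% with 30. From 30 enrolled with 15% dropout, 30 × 0.85 = 25.5 would be analysed.

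**The case against.** The strongest objection is that no section says either outcome suffices. Section 2 joins the two measures with a conjunction, and 3.6.1 names one construct. On a both-required reading there is no inflation. This stands: a reader might infer that the trial's error rate simply is 8–10%, but the documents do not support that as a fact. The figure is conditional on an either-suffices rule, and at correlation 0.9 it is about 7%. The objection does not remove the problem, because the both-required reading leaves the power statement short.

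It can also be said that Bonferroni is named, that Bonferroni-adjusted p-values are themselves compared with 0.05, and that an analysis plan not shown may add a rule. The closing sentence on alpha indeed does not by itself exclude an adjustment across outcomes. But the text ties the correction to the group-by-time analysis, and the sample size reproduces only at the full 0.05. The protocol itself also fixes two unranked primaries, so this is more than a detail left for later.

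Three stronger readings should not be drawn.

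- **Device practice.** Because "The measurement is performed using an electronic inspiratory muscle training device that applies conical flow resistance as a loading method", a reader might infer that S-index favours the training arm through practice on the device. Section 3.7 has controls train on the same device, and 3.6.1 includes a warm-up to reduce learning effects, so a between-arm advantage from familiarity is not shown.
- **Splitting alpha.** A reader might infer that a split must break the power target. That holds at 22 analysed, but at 25 power is close to 80% and at 30 it exceeds it.
- **Time point.** A reader might infer that the remedy requires a T2-only test. The two-outcome problem can be solved with the planned interaction test left in place.

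Powering on one outcome is also not an error in itself. It matters here only because the second outcome has equal standing.

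**Conclusion.** The point holds in conditional form. The protocol names two primary outcomes of equal rank, tests each at 0.05 and gives no decision rule. With an either-suffices rule, family-wise error is 9.75% for independent tests, falling to 7.0% at correlation 0.9, against a nominal 5%. With a both-required rule, error is controlled but the 80% power does not apply to the joint claim. Under neither reading are both stated design figures secured.

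This assumes two-sided tests, 1:1 allocation and one confirmatory test per outcome. The correlation is not in the document. The power figures are for the two-group comparison that reproduces the plan's 22, not for the interaction F test.

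**What to change.** Before any results are seen, state a fixed sequence. Test the planned group-by-time effect on MIP, the outcome on which the sample size was built, at two-sided 0.05. Test the same effect on S-index at two-sided 0.05 only if MIP is significant; otherwise report S-index as an estimate with a 95% confidence interval. Say in section 4 that the Bonferroni correction applies within each outcome's ANOVA, if that is what is meant. Bring the abstract, section 2 and section 3.6.1 into line with the chosen order.

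The cost is small: no extra participants, no change to the planned model and no loss of MIP power. The downside is that S-index cannot support a confirmatory claim if MIP fails. The change ranks the primary outcomes, so it needs a dated record. Section 5 says no further modifications are allowed. If an amendment is not possible, a dated analysis plan completed before the end-of-study analysis described in section 3.9 can hold the rule.

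If the investigators want either outcome to be able to succeed alone, 0.025 each is a workable alternative. It needs 26 analysed for 80% MIP power, or 26 / 0.85 = 30.6, so 31 enrolled, against the 30 planned.
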